### Sample size {14}

The participating children are expected to represent the general population and are not a clinical sample with a presumed high level of mental symptoms. Hence, even if DBED will have a promoting effect on mental health among the children, the difference between the intervention and the control group will probably be small. In the absence of other similar studies, we chose a difference of 0.8 in SDQ Total Difficulties Scale score based on discussions in the project group. Then, we powered the study to be able to detect such a difference between the implementation and the control group. Mplus was used for Monte Carlo simulations assuming the participation of 20 kindergarten (clusters) with ten participating subjects within each cluster and a baseline SDQ mean 5.5 (English norm data: 5.7) SD = 5.5 (σ^2^_within_ = 30.25). The group differences were represented with a predictor of the slope factor in a latent growth curve model. The model assumed normative stability in the controls (mean change = 0.0) and a reduction of −0.8 in the intervention group during the total period. Group sizes were set to be equal. Some between-cluster variation was specified in the intercept factor (σ^2^_between_ = 2.0) to give expected ICC = 0.10 in the six outcome variables over time. The attrition was assumed to be up to 25%. The number of replications was 1000. To achieve the difference of 0.8 with a sample size of *n* = 100 in each group, the statistical power for the testing of group difference was found to be 95%.

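### The printed variance inputs of the sample-size simulation give an ICC of about 0.06 on their plain reading, not the stated 0.10

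*Protocol article*

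**What the plan says.** All the inputs are in the Sample size {14} section of the protocol article, which describes a Mplus Monte Carlo simulation:

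- Design: "20 kindergarten (clusters) with ten participating subjects within each cluster", with equal arms.
- Outcome variability: "SD = 5.5 (σ^2^_within_ = 30.25"), for the SDQ Total Difficulties score.
- Clustering: "Some between-cluster variation was specified in the intercept factor (σ^2^_between_ = 2.0) to give expected ICC = 0.10 in the six outcome variables over time".
- Effect: "normative stability in the controls (mean change = 0.0) and a reduction of −0.8 in the intervention group during the total period".
- Tested parameter: "The group differences were represented with a predictor of the slope factor in a latent growth curve model".

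Attrition of up to 25% is assumed, and the reported power is 95% with 100 children per group. The section gives no residual variance, slope variance, within-child correlation or second between-kindergarten variance.

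**The concern.** In a two-level model the ICC of an outcome is fixed by its between and within variances. The section prints all three quantities and presents the between variance of 2.0 as the value that produces the ICC of 0.10. Put into the formula, the two variances give a clearly smaller ICC.

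Two things could be at stake. If the variances are right, the article claims a larger allowance for clustering than was simulated. If the ICC and the 2.0 are right, the simulated outcome was less variable than the SD of 5.5 implies, and the reported power could belong to that less variable outcome. The reader cannot tell which applies, and this section is the only justification given for 20 kindergartens of ten children.

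**Working it through.** **Inputs (all from Sample size {14}).** Between variance B = 2.0; within variance W = 30.25 = 5.5²; stated ICC 0.10; 100 children per arm; six outcome occasions; total slope difference 0.8.

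**1. Try to reproduce the stated ICC.** ICC = B/(B + W).

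- 30.25 as within variance, as labelled: 2.0/(2.0 + 30.25) = 2.0/32.25 = 0.062.
- 30.25 as total variance: 2.0/30.25 = 0.066.

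Neither rounds to 0.10. Child-level residual or slope variance on top of 30.25 would lower the ICC further.

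**2. What would give 0.10.**

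- Keep W = 30.25: B = 30.25/9 = 3.36.
- Keep a total of 30.25: B = 0.10 × 30.25 = 3.03.
- Keep B = 2.0: W = 9 × 2.0 = 18, a within SD of √18 = 4.24 and a total SD of √20 = 4.47.
- Keep both 2.0 and 30.25: a further 3.36 − 2.0 = 1.36 of between-level slope or residual variance, since 3.36/33.61 = 0.10. The text mentions none.

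**3. Does the between variance matter for the powered test?** The test is on the slope. A linear growth model was evaluated by generalised least squares with 20 kindergartens of ten, six equally spaced occasions, random child and kindergarten intercepts, no slope variance, no attrition and two-sided 5%. The spacing, the sidedness and the absence of slope variance are assumptions; leaving out attrition is a simplification.

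- With residual variance 1.72 and group acting on the slope only, raising B from 2.0 to 3.36 moves power from 95.3% to 95.2%.
- If a group difference in intercept is also estimated, power is 95.0% with either value.

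**4. Does the within variance matter?** With group differences in both intercept and slope, occasions coded 0 to 5 (sum of squares 17.5), a slope difference of 0.8/5 = 0.16 and wave-to-wave correlation ρ:

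z = 0.16 / √[ (W(1 − ρ)/17.5) × (2/100) ]

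- 95% power needs z = 1.960 + 1.645 = 3.605, so the residual variance is W(1 − ρ) = (0.16/3.605)² × 17.5 × 50 = 1.72.
- If W was 18, this means ρ = 1 − 1.72/18 = 0.904.
- With the same ρ and W = 30.25, z = 3.605 × √(18/30.25) = 2.78. Power is Φ(2.78 − 1.96) = Φ(0.82), about 79%.
- If 18 and 30.25 differ only in child-intercept variance, the residual variance stays at 1.72 and power stays at 95%.

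The article does not give ρ. The value 0.904 is simply the one at which this model returns the stated 95% with W = 18.

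**The case against.** The strongest reply is that the figures conflict only if the unprinted terms are zero. The 2.0 is placed in the intercept factor, while the ICC is claimed for the outcome variables. In a two-level growth model the between variance of an outcome can also include between-level slope or residual variance, and about 1.36 of it would restore 0.10. This stands as a possibility, so it would be too strong to say that no reading works. It is not the natural reading, because the sentence credits the 2.0 with producing the ICC.

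A second rescue is an ICC for the latent intercept alone: child-intercept variance 18 plus residual 12.25 sums to 30.25, and 2.0/20 = 0.10. The wording assigns the ICC to the six outcomes, not to the intercept. With a residual variance of 12.25, slope power in the model above would also be only about 30%, not 95%.

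Three stronger conclusions may tempt a reader, and the document supports none of them.

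- **That the 95% power is refuted.** The between-intercept variance has almost no effect on the slope test, and the residual and slope variances that drive its power are not printed. The 95% can be neither reproduced nor disproved from the article.
- **That effective sample size is overstated in the powered test.** The design effect for ten per kindergarten is 1 + 9 × 0.062 = 1.56 against 1 + 9 × 0.10 = 1.90. These apply to a comparison of levels at one time, which is not the test that was powered.
- **That power falls much further at lower wave-to-wave correlations.** At correlations of 0.6 to 0.8 even a within variance of 18 gives only 42% to 70% power in this model. Such correlations already contradict the stated 95% and so cannot, on these assumptions, describe the simulation that was run.

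**Conclusion.** The point holds as an inconsistency between printed inputs. On the plain reading the ICC is 0.062 (0.066 if 30.25 is the total variance), against the stated 0.10, and nothing elsewhere in the article reconciles them.

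The consequence is limited. If only the ICC is misstated, slope power moves by less than one percentage point. The stated power is affected only if a smaller within variance, and with it a smaller residual variance, was simulated. The illustrative drop from 95% to about 79% requires that 18 was used, that residual variance scales in proportion to within variance, that there is no slope variance, and that 100 children per arm are analysed without attrition. The document does not show that any of this happened; only the Mplus input can settle it.

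**What to change.** Check the Mplus input and make the three figures agree.

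- If 30.25 and 2.0 were used with no other between-level variance, either restate the ICC as about 0.06, or rerun with a between variance of 3.36 and keep the ICC at 0.10.
- If a within variance of 18 was used, rerun with 30.25 and a between variance of 3.36, and restate the resulting power at 100 per arm.
- If further between-level variance made up the difference, say so in the sentence that states the ICC.

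The cost is at most one rerun of an existing simulation and one corrected sentence. The sample size, recruitment and analysis do not change. The downside is that the stated ICC or the stated power may become less favourable.

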## Statistical methods

### Statistical methods for primary and secondary outcomes {20a}

Primary outcome:◦ Possible differences between children in intervention and control kindergartens in mental health trajectories will be estimated by Latent growth curve (LGC) models (gives equal results as linear mixed/multilevel models, given similar parameter specification). Both random intercept fixed slope and random intercept random slope will be analyzed, meaning models with no variance in change (slope) and models with individual differences in slope (random effects). Then the full unstructured matrix with random intercept, random slope, and the covariance between intercept and slope will be tested. Initially, linear change over time will be tested. If not supported with data, different non-linear change models will be explored (quadratic, cubic, piecewise growth). Then, substantial predictors will be entered into the model and analyzed. Also, within level residual structures will be tested.Secondary outcomes:◦ Possible differences between children in intervention and control kindergartens in parental stress and time to initiated locally available supportive action, respectively, will be analyzed in a similar way to the primary outcome.Process measures:◦ Factor structure will be estimated by confirmatory factor analysis (CFA).◦ Agreements between:▪ Reported concern (EWQ) and DBED concluded concern (EWQ), respectively, and mental health (SDQ): correlations (Pearson’s and Spearman), Cohen’s (weighted) Kappa, CFA: uni-, bi-, and tri-factor models representing different sources of information (parent 1, parent 2, teacher. Latent difference score (LDS) models will also be explored for common levels and differences within and between families.Parent’s and teacher’s mental health report (SDQ): correlations (Pearson’s and Spearman), CFA, including method factors, LDS models.Parents’ and teacher’s possible worries for the child: Cross table with chi-quadrat test, Cohen’s weighted Kappa, CFA, and LDS models.▪ Change from reported (EWQ) to concluded concern (EWQ) during the parent-teacher conference: cross table with chi-quadrat test, Cohen’s weighted Kappa, CFA/LDS models.▪ Satisfaction with DBED:Initial: distribution of scores and mean values of each item. Mean value of total score.Follow-up: repeated measures of mean values of each item and total scores and LGC models.▪ Predictors of mental health change, parent concern, teacher concern, parent satisfaction, parental stress: LGC models with predictors (conditional LGC models).Statistical principles◦ Level of statistical significance: We will use the threshold of *p* = 0.05 for the main analysis. However, the threshold perspective has been debated, and there is considerable literature claiming another perspective as a relevant alternative. This implies the use of exact p-values as a degree of certainty of the generalization from sample to population. In the exploratory part of the project, this practice will be used. In addition, we will calculate effect sizes to evaluate the results beyond statistical significance.◦ Adjustment for multiplicity: Detailed power analysis (Monte Carlo analysis) was used to decide sample size for satisfactory power. Adjustment is irrelevant for this analysis. Regarding other statistical analyses, analyses may introduce risk for Type 1 errors when testing family-wise tests. When testing specific hypotheses (see above), no adjustment should be necessary. When exploring differences and relations not pre-specified in hypotheses (family wise tests), Bonferroni corrections will be used.◦ Confidence intervals to be reported: 95%◦ Methods used for assumptions to be checked for statistical methods: Residuals will be saved and checked for normality and homoscedasticity. Relations will be plotted and linearity in relations evaluated.◦ Details of alternative methods to be used if distributional assumptions do not hold: Bootstrapping will be used if normality does not hold. However, larger samples are robust for such deviations.If survival models (Cox and non-proportional parametric hazard models based on Weibull distribution), the proportional assumption will be tested. In addition, covariates will also be tested as time-dependent covariates to explore whether they relate to events differently over time.

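### The stated 95% power for a 0.8-point SDQ difference does not follow from the stated inputs, and those inputs contradict the stated ICC

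*Protocol article*

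**What the plan says.** All the sizing assumptions are in the Sample size section of the protocol article.

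- **Target difference:** "we chose a difference of 0.8 in SDQ Total Difficulties Scale score based on discussions in the project group". It enters as no change in controls and "a reduction of −0.8 in the intervention group during the total period".
- **Test:** "The group differences were represented with a predictor of the slope factor in a latent growth curve model".
- **Spread:** "SD = 5.5 (σ^2^_within_ = 30.25").
- **Clustering:** 20 kindergartens of ten children, with a between-kindergarten variance of 2.0 on the intercept factor, "to give expected ICC = 0.10 in the six outcome variables over time".
- **Attrition:** "The attrition was assumed to be up to 25" per cent.
- **Result:** from 1000 Mplus replications with 100 children per arm, "the statistical power for the testing of group difference was found to be 95" per cent.

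The Outcomes section places the primary endpoint at the sixth half-yearly measurement. The section on statistical methods for primary and secondary outcomes sets the threshold at p = 0.05. It plans models without variance in change and also "models with individual differences in slope (random effects").

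**The concern.** A difference of 0.8 on an SD of 5.5 is 0.145 SD, which is small for 100 children per arm. Repeated measurement can recover much of the shortfall, but how much depends on two quantities: how strongly a child's scores correlate across waves, and how much children differ in true change. The section gives neither, so the reader cannot tell what the 95% rests on. Two of the inputs it does give, the variances and the ICC, disagree with each other.

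The figure matters for interpretation. If the trial is reported as having 95% power for 0.8 points, a non-significant result will be read as strong evidence against an effect of that size. If the real power is well under that, the reading is wrong.

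**Working it through.** **Inputs from the documents.** 100 children per arm in 20 kindergartens of ten; six waves, taken as equally spaced; total effect 0.8; within variance 30.25; kindergarten intercept variance 2.0; attrition 0 or 25%; α = 0.05, taken as two-sided.

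**Inputs assumed, because the article does not give them.** Within-child correlation across waves, r, varied from 0.5 to 0.95; slope variance zero unless stated; attrition as steady dropout reaching 25% by wave 6.

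**1. The plan's own figure.** The 95% was not reproduced by any standard reading of the stated inputs. A single comparison at one time point (SD 5.5, 100 per arm, no clustering or attrition) has 17.6% power, or 26.9% one-sided. It would need about 1229 children per arm for 95%.

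**2. What 95% would require of the slope test.** The standard error of the arm difference in total change must be 0.8/(1.96 + 1.645) = 0.222. For six waves coded 0 to 5, the time scores have a sum of squares of 17.5 about their mean. With no slope variance and no attrition,

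SE² = (2/100) × (25/17.5) × residual variance = 0.02857 × residual variance.

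The residual variance can therefore be at most 0.222²/0.02857 ≈ 1.72 out of 30.25, so r must be at least 1 − 1.72/30.25 = 0.943. With 25% attrition the requirement rises to about 0.954. The kindergarten intercept variance hardly affects this test.

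**3. Power at assumed correlations.** Without attrition at r = 0.6 the residual variance is 0.4 × 30.25 = 12.1, SE = √(0.02857 × 12.1) = 0.588, and power is Φ(0.8/0.588 − 1.96) = 27%. Generalised least squares for the full three-level model gives the ranges below; each runs from free to equal baseline means, with zero slope variance.

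| r (assumed) | Variance 30.25, no attrition | 30.25, 25% attrition | Variance 18, no attrition | 18, 25% attrition |
|---|---|---|---|---|
| 0.5 | 23–26% | 20–22% | 35–38% | 30–32% |
| 0.6 | 27–30% | 23–25% | 42–45% | 36–38% |
| 0.7 | 35–37% | 29–31% | 53–55% | 45–47% |
| 0.8 | 49–50% | 41–42% | 70–72% | 61–62% |
| 0.9 | 78–79% | 68–69% | 94–95% | 89% |
| r needed for 95% | 0.94 | 0.95 | 0.90 | 0.92 |

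**4. Slope variance.** Take variance 30.25 and r = 0.95. If the SD of true change over the whole period is 1.5 points (variance 2.25, assumed), power falls to about 69% with attrition and 77% without. With a variance of 3 it is 62% and 70%.

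**5. The ICC.** The stated variances give 2.0/(2.0 + 30.25) = 0.062. An ICC of 0.10 needs a between variance of 30.25 × 0.10/0.90 = 3.36, or a within variance of 2.0 × 0.90/0.10 = 18. The first leaves the slope test almost unchanged. The second is the favourable branch, shown in the two right-hand result columns.

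**6. Detectable difference.** With 80% power this is (1.96 + 0.84) × SE. With 25% attrition, no slope variance and free baseline means, the SE at r = 0.7 and 0.6 is 0.566 and 0.651 for variance 30.25, giving about 1.6 and 1.8 points. For variance 18 it is 0.436 and 0.502, giving about 1.2 and 1.4.

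**The case against.** The strongest reply is that a reader might infer from this that 95% power is impossible, and the documents do not support that. The threshold itself shows that 95% is attainable at a correlation of about 0.94–0.95, or 0.90–0.92 if the within variance is 18, provided slopes do not vary. The article gives neither the residual nor the slope variance, so such values are not excluded. Nor does it say how the 30.25 was divided between stable and residual parts. This stands, and the point is limited to non-reproducibility.

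A reader might equally infer that the plan's own inputs yield a power of 20–50%. They do not: that range needs a correlation the article does not give, and the branch with variance 18 runs higher, to about 72%.

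Three further replies have partial force. The methods section lists fixed-slope as well as random-slope models, so it does not prove that the simulation needed slope variance. A journal article need not print every simulation input, and the full protocol is available on request, so the omission alone is no fault. The Discussion admits that the power estimate rests on an uncertain assumption and expects more than 100 + 100 children. That admission concerns which difference is meaningful, not the variance or the correlation, and a modest excess does not close a gap of this size.

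It is also tempting to infer a time-scaling slip. Entering 0.8 per year (2.0 points over 2.5 years) would give about 83–96% at correlations of 0.5–0.7 with attrition. But the text says the reduction applies to the whole period, and nothing in the document shows that a slip occurred. It is a reason to check the coding, no more.

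**Conclusion.** The point holds in this form. The 95% is not reproducible from what the section states, and it requires an undisclosed and very high within-child correlation (about 0.90–0.95, depending on variance and attrition) together with no individual differences in true change. For assumed correlations of 0.5–0.8 and no slope variance, power for 0.8 points is about 20–50% with within variance 30.25 and about 30–72% with 18. Any slope variance lowers these figures. The power ranges rest on the assumed correlations, equal spacing, steady dropout and a two-sided test.

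The contradiction between the variances (0.062) and the stated ICC (0.10) needs no assumption at all. Because of it, no single power value follows from the section as written.

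**What to change.** 1. Reconcile the ICC of 0.10 with the variances 2.0 and 30.25, and say which of the three was used in the simulation.
2. Rerun the simulation with the time scores, residual variance, child slope variance and attrition pattern written out, and check that −0.8 is coded as the change over the total period.
3. Replace 95% with the power obtained for 0.8. Alternatively, keep 100 + 100 and state the difference detectable with 80% power together with the correlation and variances it assumes. With 25% attrition and no slope variance this is about 1.6–1.8 points at assumed correlations of 0.7–0.6 for within variance 30.25, and about 1.2–1.4 for 18.
4. Unless the rerun supports high power, state that a non-significant result does not exclude a 0.8-point difference.

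The cost is one rerun, a reworded paragraph and probably a less favourable figure. No extra enrolment is needed.

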### Recruitment {15}

By collaboration agreements, the three kindergarten organisations through their kindergarten managers have committed to facilitate recruitment of participants. Members of the project group have offered extensive information and training for teachers and parents in all kindergartens (see under the “ Strategies to improve adherence to interventions {11c}” section). A QR code linking to registration for potential participating parents is available in fliers and in the meetings with eligible parents. Consenting parents are offered two cinema tickets. During the recruitment period, the managers of every participating kindergarten are given feedback as to the consent rate in their own kindergarten compared to all the others’. Recruitment will continue every new kindergarten year (August to July) until consent is achieved from a minimum of 100 children in each arm.

## Assignment of interventions: allocation

### Sequence generation {16a}

To prevent contamination from intervention to control cases, the separate kindergartens will be assigned to either intervention or control condition. Because the kindergartens will be recruited from three different organisations, randomizing will be performed within each organisation (block randomisation). The randomisation will be computer-generated by a staff member at Research Unit for Health Surveys, University of Bergen, who is not a part of the PRO-DIALOG project.

### Concealment mechanism {16b}

N/a. To prevent contamination from intervention to control cases, the informed consent to the participants in the control kindergartens will not contain the same detailed information about DBED as the participants in the intervention kindergartens. Hence, intervention and control conditions were assigned at the kindergarten level before the recruitment of parents. To be able to motivate parents to participate, kindergarten teachers in the intervention kindergartens were trained in the DBED method before recruitment. The kindergarten managers were informed about the allocation about 6 months before recruitment.

